### Objective and hypothesis

The objective of this trial is to evaluate the feasibility, short-term safety, long-term oncological safety, and potential benefits of SILS plus one compared with CLS for the radical resection of rectosigmoid cancer in a randomized controlled trial. The hypothesis is that SILS plus one is feasible for the radical resection of rectosigmoid cancer and offers short-term safety and long-term oncological safety comparable to that of CLS. In addition, SILS plus one provides better cosmetic results and faster convalescence compared with CLS.

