### Statistical methods

#### Sample size

The sample size was determined for the primary endpoint: early morbidity measured on POD 30. Based on our database, the early morbidity rate of CLS for colorectal cancer is 15.2 %; for SILS plus one for colorectal cancer, the early morbidity rate is 11.1 %. The sample size was determined according to the following:Hypothesis: the early morbidity of SILS plus one is not higher than that of CLS (noninferiority analysis).We set the noninferiority margin at 10 %.A one-sided analysis with a type I error (α) of 2.5 % and a power (1-β) of 0.80 was assumed.

Based on these assumptions, a sample size of 90 participants per arm was calculated using the NCSS-PASS (11^th^ edition, NCSS, LLC, Utah, USA). Assuming a drop-out rate of 10 %, the total number of participants needed per arm is 99, resulting in a total of 198 participants for the primary aim.

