#### Statistical analysis

The statistical analysis will be performed using SPSS version 13.0 (SPSS, Inc., Chicago, IL, USA). A two-sided p < 0.05 will be considered significant. Descriptive statistics will be used for baseline characteristics. For categorical variables, including the primary outcome, a χ^2^ test or Fisher’s exact test will be applied. For continuous variables, Student’s t test or the Mann-Whitney U-test will be applied. Kaplan-Meier curves and the log-rank test will be used to analyze the OS and DFS differences between the two groups. We do not plan to perform interim analyses. Missing values will not be imputed. Any outcomes of interest analysis will be performed based on the intention-to-treat population and per-protocol population (PPP), and a standard sensitivity analysis will be performed based on the PPP.

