Oncological safety is an important measurement for a new surgical technique in the field of radical cancer resection, and the most powerful evidence of oncological safety is the long-term DFS and OS. In 2014, a case-match study compared 27 SILS patients with 27 CLS patients treated for colorectal cancer, and the 5-year local recurrence rate was 3.7 % versus 0 (p = 0.55), the distant metastasis rate was 14.8 % versus 3.7 % (p = 0.15), and the OS was 92.6 % versus 96.3 % (p = 0.66) for SILS and CLS, respectively [35]. In the same year, in a propensity-score matching analysis, Kim et al. compared SILS (n = 60) with CLS (n = 120) for sigmoid cancer. The 3-year DFS was 89.5 % and 87.4 % (p = 0.751), and the OS was 94.5 % and 97.1 % (p = 0.223) for SILS and CLS, respectively [14]. As the cases and follow-ups accumulated, Yun et al. recently reported that SILS (n = 239) colorectomy showed an equivalent of 48 months DFS (89.8 % versus 89.9 %, p = 0.548) and OS (98.7 % versus 98.6 %, p = 0.971) compared with CLS (n = 239) for colon cancer [1]. Although these three studies suggest that the oncological safety of SILS is comparable to that of CLS for colorectal cancer, the retrospective design, small samples and poor methodological quality of these studies might have resulted in selection bias and evaluation bias, which would largely reduce the believability of the study results. Considering all of the above reasons, it is necessary to evaluate the oncological safety of SILS plus one for rectosigmoid cancer using the 3-year DFS and the 5-year OS. Evaluating the long-term DFS and OS of patients with colorectal cancer requires long-term follow-up; consequently, the assessment of the pathological outcomes (such as the tumor size, length of the proximal and distal resection margins, and the number of harvested lymph nodes removed) of each specimen is essential for predicting oncological safety.

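### The plan hypothesises comparable long-term oncological safety, but the only DFS and OS comparison it fixes is a log-rank test of difference, which cannot show comparability

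*Protocol article*

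**What the plan says.** The Objective and hypothesis section states that SILS plus one "offers short-term safety and long-term oncological safety comparable to that of CLS", and the abstract repeats this. The Discussion says that "the most powerful evidence of oncological safety is the long-term DFS and OS" and that "it is necessary to evaluate the oncological safety of SILS plus one for rectosigmoid cancer using the 3-year DFS and the 5-year OS".

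The Statistical analysis section gives one sentence to these endpoints: "Kaplan-Meier curves and the log-rank test will be used to analyze the OS and DFS differences between the two groups". The general rule in the same section is "A two-sided p < 0.05 will be considered significant".

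The only margin in the document, 10 %, is in the Sample size section, which opens with "The sample size was determined for the primary endpoint: early morbidity measured on POD 30". No margin, event number or hazard-ratio interval is stated for DFS or OS. Both are listed as secondary endpoints.

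**The concern.** The null hypothesis of a log-rank test is that the two survival curves are equal. A small p-value is evidence of a difference. A large one means only that no difference was shown, which happens when the arms are alike and also when there are too few events to tell. A claim of comparability needs an estimate whose confidence interval excludes a difference regarded as unacceptable. The stated test therefore does not fit the stated hypothesis.

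The risk of misreading is practical. The Discussion lists three retrospective studies by their non-significant p-values and says they suggest comparable oncological safety. One had 27 patients per arm, with distant metastasis of 14.8 % after SILS against 3.7 % after CLS (p = 0.15). That is a fourfold difference against SILS, counted on the side of comparability. The Discussion does caution about the design, size and quality of these studies. Randomization removes the selection bias but not the imprecision: this trial's 198 patients compare with 180 and 478 in the two larger studies.

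The Risk-benefit ratio section itself names uncertain oncological outcomes as a risk of SILS, so false reassurance would matter to patients and surgeons.

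**Working it through.** **The plan's own figure.** The Sample size section states that "the early morbidity rate of CLS for colorectal cancer is 15.2" % and that for SILS plus one "the early morbidity rate is 11.1" %, with a margin of 10 points, one-sided α of 2.5 % and power of 80 %. The distance to the margin is 0.10 + (0.152 − 0.111) = 0.141.

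n per arm = (1.960 + 0.842)² × (0.111 × 0.889 + 0.152 × 0.848) / 0.141² = 7.849 × 0.2276 / 0.01988 = 89.8, so 90 as stated. Adding 10 % gives 99 per arm and 198 in total. This calculation concerns early morbidity only.

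**Inputs for DFS and OS.** The protocol gives no event numbers, so these are assumptions:
- Patients: 198, or 198 × 0.90 = 178 after the planned drop-out.
- DFS, from studies cited in the Discussion: 87.4 % and 89.5 % at 3 years; 89.8 % and 89.9 % at 48 months. Using the 48-month rates as 3-year rates slightly overstates the 3-year events, which favours the plan.
- OS at 5 years: 92.6 % and 96.3 %, from the study with 27 patients per arm, where one patient is 3.7 points.

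**Precision by 3 years if the arms are equal.** Events D = N × (1 − S), from 178 × 0.101 = 18.0 to 198 × 0.126 = 24.9. With SE(log HR) = 2/√D and an observed HR of 1.0, the upper 95 % limit is exp(1.96 × 2/√D):
- D = 18: 2.52
- D = 25: 2.19

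The 95 % half-width for the 3-year DFS difference, 1.96 × √(2S(1 − S)/n), runs from 8.4 points (S = 0.899, n = 99) to 9.8 points (S = 0.874, n = 89).

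**All five years of follow-up.** At constant hazard S(5) = S(3)^(5/3), which is 0.837 for 0.899 and 0.799 for 0.874. Events are 178 × 0.163 = 29 to 198 × 0.201 = 40, and the upper limit at an observed HR of 1.0 is 2.07 to 1.86.

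**Power by 3 years if the hazard is truly doubled.** The control arm keeps S and the SILS plus one arm has S².
- Low end: 89 × 0.101 + 89 × (1 − 0.899²) = 9.0 + 17.1 = 26 events.
- High end: 99 × 0.126 + 99 × (1 − 0.874²) = 12.5 + 23.4 = 36 events.

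Power = Φ(ln 2 × √D/2 − 1.96) = 42 % to 55 %. A true doubling would thus give p > 0.05 in about 45 to 58 % of trials.

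**OS.** Deaths: 178 × 0.037 = 6.6 to 198 × 0.074 = 14.7. The upper limit at an observed HR of 1.0 is 4.6 to 2.8.

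**When p > 0.05 alone would exclude a doubling.** The largest non-significant HR is exp(1.96 × 2/√D), and its upper limit is the square of that. For this to stay below 2, D must exceed (2 × 3.92/ln 2)² = 128 events. No scenario above comes near that number.

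**The case against.** The strongest reply is that the article nowhere says a non-significant result will be read as proof of safety. That is correct. A reader might infer such a rule from the hypothesis and the single stated test, but the documents do not contain it. What can be said is that the stated analysis leaves room for that reading.

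Second, DFS and OS are secondary, the trial is sized for early morbidity, and nobody claims power for survival. This also stands: low power for DFS is not in itself a fault. Nor is the bare absence of a hazard ratio or interval, which an article may leave to the full protocol or analysis plan. Kaplan-Meier curves do yield 3-year and 5-year estimates per arm. What remains is that the article states a hypothesis of comparability and pairs it with a test that cannot support it.

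Third, it is tempting to say that the trial has almost no ability to detect oncological harm, or that non-significance is likely whatever the truth. The figures do not bear this out. Keeping the event count at its equal-arms value gives only 31 to 41 % power at HR 2, but that ignores the extra events in the worse arm; counting them gives 42 to 55 %. On the same basis a true HR of 3 would be detected about 90 % of the time.

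Fourth, whether a doubled hazard is excluded at an observed HR of 1.0 depends on the event count. About 32 events suffice, since (3.92/ln 2)² = 32, and five years of follow-up might supply them. The statement that a doubling cannot be excluded therefore holds by 3 years under the cited rates, not without condition.

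**Conclusion.** The point holds as a mismatch between a stated hypothesis and a stated method. Comparable long-term oncological safety cannot be concluded from a log-rank test of difference, and the only margin in the plan belongs to another endpoint.

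On the assumed rates, the 3-year data would leave hazard ratios up to about 2.2 to 2.5 compatible with an observed ratio of 1.0, and a true doubling would be missed roughly half the time. With five years of follow-up the upper limit falls to about 1.9 to 2.1. The OS limits of about 2.8 to 4.6 rest on a very small study and are fragile. All event counts are assumptions taken from cited retrospective rates. The main conclusion does not depend on them, because p > 0.05 alone would exclude a doubling only above about 128 events.

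The documents do not support the further inference that the investigators have committed themselves to calling a non-significant result safe. Since the endpoints are secondary and the remedy is wording, this should be corrected but does not threaten the primary analysis.

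**What to change.** In the Statistical analysis section, make these the main long-term results, each with a 95 % confidence interval: the hazard ratios for DFS and OS, the difference in 3-year DFS, and the difference in 5-year OS. Keep the Kaplan-Meier curves, and treat the log-rank p-value as supportive.

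State in advance that comparability will be claimed only if the interval excludes a difference that has been named and clinically justified beforehand. Otherwise the oncological results are to be reported as descriptive and inconclusive, whatever the p-value. Align the wording of the hypothesis in the abstract and in the Objective and hypothesis section.

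This needs no extra patients, visits or measurements. The cost is a more modest long-term claim: with a half-width of about 8 to 10 points on the 3-year DFS difference, a margin narrower than that could be met only if the observed result favoured SILS plus one.

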### Ethical considerations

The study will be performed according to the Declaration of Helsinki [42] and the ICH GCP E6 guidelines [41]. The Medical Ethics Committee of Nanfang Hospital reviewed and approved this study on March 19, 2014 (reference number: NFEC-2014-026). The Medical Ethics Committee of Nanfang Hospital will be informed of significant protocol amendments.

Only the patients who signed the informed consent will be included in the study. The participants will be informed that the participation in the trial is voluntary and that they can withdraw consent at any time without giving reasons.

### Dissemination policy

This trial is intended for publication in international peer-reviewed journals. The results of this study will also be presented at internationally relevant scientific meetings. The progress and the results of the study will be saved at Clinicaltrials.gov to allow general access to documented findings.

### Registration

This trial was registered with ClinicalTrials.gov (https://www.clinicaltrials.gov/ct2/show/NCT02117557?term=single&cond=colon+cancer&cntry1=ES%3ACN&rank=11) under the registration number NCT02117557 on April 16, 2014.

### Protocol version

This manuscript refers to the second version of the full study protocol issued on 20 December 2013. Protocol modifications will be reported to all investigators, the MEC, all trial participants, and the journal.

## Discussion

Although the SILS plus one technique has been adopted in clinical use because it provides most of the benefits of SILS and CLS and minimizes the risks associated with SILS [15, 17], as far as we know, there are only two large-scale randomized controlled trials with more than 100 samples comparing SILS with CLS for colorectal cancer treatment. One is the SILVERMAN1 trial for right colonic cancer [43], and the other is the Multicenter Single-Port Colectomy trial for colon adenocarcinoma excluding distal transverse colon cancer, splenic flexure colon cancer, and descending colon cancer [44]. There are no published results. To the best of our knowledge, no large-scale RCT has focused on the risks and benefits of SILS plus one compared with CLS for rectosigmoid cancer treatment.

Early morbidity was chosen as a primary endpoint of this trial because early morbidity is an indication of short-term safety, which is a prerequisite for the general clinical application of a new surgical technique [14]. Moreover, early morbidity is a measure of surgical recovery for patients undergoing major abdominal surgery [28]. Among all types of early morbidities, we will focus on intra-abdominal morbidity and trocar-related morbidity, including intraoperative morbidity (such as injuries and bleeding during surgery) and 30-day postoperative morbidity (such as anastomotic leakage, anastomotic bleeding, intro-abdominal bleeding, incision complications and trocar-related complications). If the morbidity differs between SILS plus and CLS for rectosigmoid cancer, the technical difficulties (such as limited instrument movement, loss of triangulation, difficulty with rectal transection and intracorporeal double-stapling of anastomoses) and the different trocar numbers may be the main reasons. Moreover, the operation time and estimated blood loss during surgery have also been used to evaluate the safety of surgical techniques.

Oncological safety is an important measurement for a new surgical technique in the field of radical cancer resection, and the most powerful evidence of oncological safety is the long-term DFS and OS. In 2014, a case-match study compared 27 SILS patients with 27 CLS patients treated for colorectal cancer, and the 5-year local recurrence rate was 3.7 % versus 0 (p = 0.55), the distant metastasis rate was 14.8 % versus 3.7 % (p = 0.15), and the OS was 92.6 % versus 96.3 % (p = 0.66) for SILS and CLS, respectively [35]. In the same year, in a propensity-score matching analysis, Kim et al. compared SILS (n = 60) with CLS (n = 120) for sigmoid cancer. The 3-year DFS was 89.5 % and 87.4 % (p = 0.751), and the OS was 94.5 % and 97.1 % (p = 0.223) for SILS and CLS, respectively [14]. As the cases and follow-ups accumulated, Yun et al. recently reported that SILS (n = 239) colorectomy showed an equivalent of 48 months DFS (89.8 % versus 89.9 %, p = 0.548) and OS (98.7 % versus 98.6 %, p = 0.971) compared with CLS (n = 239) for colon cancer [1]. Although these three studies suggest that the oncological safety of SILS is comparable to that of CLS for colorectal cancer, the retrospective design, small samples and poor methodological quality of these studies might have resulted in selection bias and evaluation bias, which would largely reduce the believability of the study results. Considering all of the above reasons, it is necessary to evaluate the oncological safety of SILS plus one for rectosigmoid cancer using the 3-year DFS and the 5-year OS. Evaluating the long-term DFS and OS of patients with colorectal cancer requires long-term follow-up; consequently, the assessment of the pathological outcomes (such as the tumor size, length of the proximal and distal resection margins, and the number of harvested lymph nodes removed) of each specimen is essential for predicting oncological safety.

As an essential principle of enhanced recovery, minimally invasive surgery has been championed by a growing number of surgeons [24]. It seems obvious that the SILS plus one technique will enhance recovery compared with CLS by reducing abdominal trauma; however, as the evidence accumulated, there were arguments over whether the reduction of trocar incision is enough to enhance patients’ recovery [1, 13, 14, 34, 45]. To settle the arguments, we will use pain intensity, duration of hospital stay, time to first ambulation, bowel function (time to first flatus), eating habits (time to resuming liquid diet and soft diet) and inflammatory and immune responses (WBC, NE %, CRP, IL-6 and TNF-α) to evaluate patients’ recovery after abdominal surgery [28]. Among the above-mentioned measurements, pain is the most commonly reported symptom and the most subjective one [28]. To transform subjective pain into an objective score, we will use the VAS scale, which is the most sensitive pain scale; compared with the Numerical Rating Scale and the Four-point Verbal Rating Scale, it can discriminate between small changes in pain intensity [46]. We decided to measure patient pain intensity at rest because doing so may eliminate the effect of different levels of mobility on pain intensity. Additionally, we will record the use of additional postoperative analgesics for breakthrough pain, which will influence pain intensity, for further analysis.

The cosmetic advantage of SILS plus one over CLS seems obvious, and it seems to be a permanent advantage of SILS plus one. However, at present, no study available assesses whether reducing the use of abdominal trocars will affect body image, cosmesis, and patient self-confidence. We will use the BIQ to evaluate the patient’s subjective feelings about the cosmesis, and we will use photographs of the incision and the length of incision to supplement the cosmesis evaluation [38].

This trial has potential limitations. 1) The trial will take place in only one center, which may impact participant recruitment or limit the generalizability of the results to other hospitals. 2) The surgeons, participants, and investigators who record the surgical information, photograph the incisions, change the wound dressings, and perform the study visit after each participant’s discharge will be aware of the group assignment, which may cause biased estimates of the treatment effect. However, because of the special nature of nonpharmacologic trials, it is impossible to blind the surgeon [47]. Although in this trial, the surgeons, the investigators mentioned above, and the participants are not blinded, the pathologists, statistician, and investigators who evaluate the unfixed specimens and perform the study visits during the patients’ hospital stays will be blinded to the group assignment. Moreover, the participants, surgeons, and investigators will not be allowed to reveal the group assignments to the others. These rules can reduce the treatment effect estimation bias.

Despite its increasing clinical application, the risks and benefits of SILS plus one for rectosigmoid cancer remain unclear. This trial is the first study to compare SILS plus one with CLS for the radical resection of rectosigmoid cancer in a large-scale, randomized, controlled trial setting. The results of this trial will provide valuable clinical evidence for the objective assessment of the feasibility, short-term safety, long-term oncological safety, and potential benefits of SILS plus one compared with CLS for the radical resection of rectosigmoid cancer.

### Trial status

The trial recruitment started in April 2014. As of June 18, 2015, 82 patients have been registered and randomized.

## Abbreviations

AEs: adverse events
AJCC: American Joint Committee on Cancer
BIQ: Body Image Questionnaire
CA 72-4: carbohydrate antigen 72-4
CA 19-9: carbohydrate antigen 19-9
CEA: carcinoembryonic antigen
CI: chief investigator
CLS: conventional laparoscopic surgery
CRF: case report form
CRP: C-reactive protein
CT: computed tomography
CTCAE: Common Terminology Criteria for Adverse Events
DFS: disease-free survival
EORTC: European Organization for Research and Treatment of Cancer
ERAS: Enhanced Recovery After Surgery
EUS: endoscopic ultrasonography
ICH: International Conference on Harmonisation
IL-6: interleukin-6
IPSS: International Prostatic Symptom Score
MEC: Medical Ethics Committee
NE %: neutrophil percentage
OS: overall survival
POD: postoperative day
PPP: per-protocol population
QLQ-C30: Quality of Life Questionnaire-Core 30
QLQ-CR29: Quality of Life Questionnaire-Colorectal 29
SAEs: serious adverse events
SILS: single-incision laparoscopic surgery
SILS plus one: single-incision plus one port laparoscopic surgery
TASGS: The Accordion Severity Grading System
TNF-α: tumor necrosis factor-α
VAS: visual analogue scale
WBC: white blood cells
